### **3.3.1.2 Three Years Primary Efficacy Parameter**

The long-term primary efficacy variable - i.e. measured GFR total slope – will be assessed with a linear regression analysis and compared with the Wilcoxon rank-sum test. Exploratory linear mixed-models using SAS PROC MIXED will be also used measured GFR repeated measures, with age, gender and baseline measured GFR as covariates. Between-groups differences in median GFR slopes and their 95% CI were determined by means of Hodges-Lehmann Estimation using the SAS PROC NPAR1WAY. Summary statistics, namely mean (sd), median, q1, q3, minimum, and maximum for measured GFR will be tabulated by nominal visit and treatment group. Moreover, relevant summary statistics will be presented for measured GFR total slope (overall and according to stratum CCC absent or stratum CCC present).

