##### **Full Analysis Set**

This set will consist of all patients randomised to receive study medication in the ALADIN 2 study.

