### **3.2 ANALYSIS SPECIFICATIONS**

Assumptions underlying all parametric analyses will be checked and transformations to normality (e.g. log-transformation) or non-parametric methods used, where violations of assumptions are seen.

For efficacy analyses based on the Full Analysis Set, no imputation of missing values will be performed. The last available data value will be used to calculate the time to onset of an event.

For both the analyses based on the Full Analysis Set and the Per Protocol Set, visit windows will not be used and data points will be classified according to the named (nominal) visit.

All statistical tests will be two-sided unless otherwise stated.

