#### **3.3.2.1 Chronic Slope of mGFR, eGFRmdrd and eGFRckd-epi (Tables 3.2, 3.52, 3.53)**

The chronic slope of mGFR, eGFRmdrd and eGFRckd-epi will be calculated from six months onward and described by the slope calculated for each patient using linear regression. Relevant summary statistics and the results of the analyses will be presented in Tables 3.2, 3.52 and 3.53.

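### The 3-year primary rank-sum test on per-patient GFR slopes ignores the randomisation stratum, the collected covariates and series length, and cannot include a patient with a single GFR

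*Supplement*

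**What the plan says.** SAP 3.3.1.2 names the measured GFR (mGFR) total slope as the long-term primary variable; it "will be assessed with a linear regression analysis and compared with the Wilcoxon rank-sum test". The effect estimate matches the test: "Between-groups differences in median GFR slopes and their 95% CI were determined by means of Hodges-Lehmann Estimation". That section does not say that a slope is fitted for each patient. The rank-sum test, the Hodges-Lehmann estimate and the median with interquartile range in the Table 3.2 template all require it, and the chronic-slope section says so for chronic mGFR: "described by the slope calculated for each patient using linear regression". No weighting, minimum number of GFR values or minimum follow-up is given.

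Covariates appear only in a secondary role: "Exploratory linear mixed-models using SAS PROC MIXED will be also used measured GFR repeated measures, with age, gender and baseline measured GFR as covariates". The randomisation stratum (presence or absence of concomitant clinical conditions, CCC) is used for separate tabulations and curves, but not in this test.

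The Full Analysis Set is primary (SAP 2.1) and is defined as everyone randomised: "This set will consist of all patients randomised to receive study medication". On missing data, SAP 3.2 states: "For efficacy analyses based on the Full Analysis Set, no imputation of missing values will be performed".

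**The concern.** This test gives the trial's answer on renal function, and it leaves information unused in three ways.

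- **Stratum and covariates.** SAP section 1 stratifies randomisation on conditions chosen because they could alter the speed of renal function loss, which is the outcome measured here. The test ignores that stratum. It also ignores age, gender and baseline GFR, although the 1-year primary analysis (3.3.1.1) adjusts for age, gender and baseline kidney volume, and the Cox models (3.3.3.1) for age, gender and baseline serum creatinine.
- **Series length.** Patients enter with estimated GFR 15-40. The withdrawal table template has a row for ESRD, and the CRF discontinuation and trial-end forms have a dialysis date. Some series will be short, yet a slope from two values counts the same as one from seven.
- **Patients with no slope.** SAP 2.3 foresees study durations under 3 months, before the first post-baseline GFR at month 6. Such a patient has no slope. No rule says what happens, and the primary set is all randomised patients.

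At stake are the power of the test, the width of its interval, and a selection after randomisation that could differ by arm.

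**Working it through.** The documents give no sample size, effect, SD or dropout rate for the 3-year endpoint, so there is no planned figure to reproduce.

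**1. Schedule.** SAP section 1 plans mGFR at month 0 and every 6 months. The CRF has the clearance form at visits 2, 4, 6, 8, 10, 12 and 14. A complete series is seven values at t = 0, 0.5, ..., 3 years.

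**2. Precision of one slope.** For independent errors with equal SD σ, Var(slope) = σ²/Sxx, with Sxx = Σ(t − mean t)².

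- Months 0 and 6: Sxx = 2 × 0.25² = 0.125.
- Seven values: Sxx = 2 × (1.5² + 1² + 0.5²) = 7.0.
- Variance ratio: 7.0/0.125 = 56.

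| Values | Last month | Sxx | Variance relative to 7 values | SE in units of σ |
|---|---|---|---|---|
| 2 | 6 | 0.125 | 56 | 2.83 |
| 3 | 12 | 0.5 | 14 | 1.41 |
| 4 | 18 | 1.25 | 5.6 | 0.89 |
| 5 | 24 | 2.5 | 2.8 | 0.63 |
| 6 | 30 | 4.375 | 1.6 | 0.48 |
| 7 | 36 | 7.0 | 1 | 0.38 |

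One value gives Sxx = 0, so no slope exists.

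**3. Adding true variation between patients.** With between-patient slope SD τ, the total variance ratio of a two-value to a seven-value slope is (τ² + σ²/0.125)/(τ² + σ²/7). Both ranges here are assumptions: τ 1.5 to 3 ml/min/1.73m² per year and σ 1 to 4 ml/min/1.73m².

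- τ = 3, σ = 1: (9 + 8)/(9 + 0.14) = 1.9.
- τ = 1.5, σ = 4: (2.25 + 128)/(2.25 + 2.29) = 28.7.

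**4. Effect on power (illustration).** Assumptions, none from the documents: 50 per arm, τ = 2, σ = 1.5 or 3, stopping unrelated to outcome, and early stoppers equally likely to have 1, 2, 3 or 4 values. Two-sided alpha of 0.05 is also assumed; the SAP states that threshold only in footnotes to the hazard-model tables. The effect was set for 80% power with complete data: δ = (1.96 + 0.84) × √[(2/50)(τ² + σ²/7)], giving 1.16 for σ = 1.5 and 1.29 for σ = 3. The comparator weights each slope by 1/(τ² + σ²/Sxx), as a stand-in for a random-slope mixed model. There were 3,000 simulated trials per setting for power and 2,000 under the null.

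| Early stopping | σ | Wilcoxon, unweighted | Precision-weighted |
|---|---|---|---|
| 0% | 1.5 | 79% | 82% |
| 0% | 3 | 78% | 80% |
| 20% | 1.5 | 69% | 76% |
| 20% | 3 | 64% | 74% |
| 40% | 1.5 | 59% | 67% |
| 40% | 3 | 48% | 64% |

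Rejection under the null was 4.1% to 5.7% across both methods.

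**5. Patients without a slope.** Under that stopping pattern one early stopper in four has a single value: 20% × 1/4 = 5% of those randomised, or 40% × 1/4 = 10%.

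**6. Stratum.** The documents give neither stratum sizes nor slopes by stratum, so the gain from stratifying cannot be put in numbers.

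**The case against.** The planned method is defensible. It prespecifies one variable, one test and a matching interval. Null rejection stays near 5% when stopping is alike in both arms. Ranking caps the influence of wild short slopes. Equal weighting also avoids down-weighting fast progressors: if stopping depends on the true slope, as ESRD may make it, precision weighting can itself bias the mean slope. All of this stands.

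The size of the loss can also be overstated. The 56-fold ratio counts measurement error only. The simulation uses normal slopes, known variances and uninformative stopping, which suits the weighted method, and 2 to 3 points of the gap remain with no early stopping. The ESRD row is an empty template with no rate, and the CRF records drug discontinuation and trial end separately, so GFR measurement need not end with treatment.

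A reader might infer four stronger points that the documents do not support:

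- **That the test is invalid.** Nothing here shows a wrong error rate.
- **That the mixed model must replace it as primary.** That is a trade-off. The model relies on missing-at-random, and a baseline-only patient adds almost no information on slope.
- **That baseline GFR is both covariate and response in the mixed model.** SAP 3.3.1.2 does not say whether baseline is in the response. The model is underspecified, not shown to be wrong.
- **That slopes should need at least three GFRs.** Under the assumed pattern with 20% stopping early, this would exclude 20% × 2/4 = 10% of patients instead of 5%, enlarging the exclusion at issue.

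**Conclusion.** The concern holds as one of efficiency and completeness. The primary test leaves out the randomisation stratum and covariates already collected, weights slopes of very different precision equally, and has no rule for patients without a slope despite a primary set of all randomised patients.

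The 56-fold ratio needs only the planned schedule and equal, independent errors. It is the extreme contrast between two individual slopes, not the loss for the trial. In the illustration that loss is 7 to 10 power points at 20% early stopping and 8 to 16 at 40%. It falls if few patients stop early, or if true slopes vary widely relative to measurement error. Selection bias is possible only to the extent that patients without a slope differ by arm, which cannot be judged from the plan.

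**What to change.** - Keep the rank-sum test and Hodges-Lehmann estimate as primary, but stratify both by CCC stratum (van Elteren test). Set no minimum of three GFRs.
- Raise the mixed model from exploratory to a prespecified key supporting analysis in all randomised patients. Specify a random intercept and slope, all mGFR values at actual dates, baseline in the response only, a treatment-by-time effect, and CCC stratum, age and gender with their time interactions, so that they act on slope as well as level.
- Report by arm how many randomised patients have no slope.
- Add a sensitivity analysis for stopping due to ESRD or death.

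The cost is SAP wording and slightly more analysis. No new data are needed, and SAP section 1 already provides for a review of the plan at blind review. The mixed model's reliance on missing-at-random remains; the retained rank test helps to check it.

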## **3.3.2 Secondary Efficacy Parameters**

### **3.3.2.1 Blood Pressure, Pulse Rate and Weight (Tables 3.3.1 to 3.7.3)**

Summary statistics, namely mean (sd), median, q1, q3, minimum, and maximum for the mean systolic and mean diastolic blood pressure, mean arterial pressure, pulse rate and weight, will be tabulated by nominal visit and treatment group.

### **3.3.2.2 Serum Creatinine (Tables 3.8.1-3.8.3)**

Summary statistics, namely mean (sd), median, q1, q3, minimum, and maximum for serum creatinine, will be tabulated by nominal visit and treatment group.

### **3.3.2.3 Hematochemistry (Tables 3.9.1 3.25.3)**

Summary statistics, namely mean (sd), median, q1, q3, minimum, and maximum for Urea, Sodium, Potassium, Calcium, phosphorus, GOT, GPT, GGT, Alkaline phosphatase,

total bilirubin, Direct Bilirubin, glucose, HbA1c, Uric Acid, Total Proteins, Albumin and IGF1 will be tabulated by nominal visit and treatment group.

#### **3.3.2.4 Creatinine Clearance (Tables 3.26.1 to 3.26.3)**

Summary statistics, namely mean (sd), median, q1, q3, minimum, and maximum for Proteins, Creatinine, Creatinine Clearance, Sodium, Urea, Glucose, Phosphate and Osmolality will be tabulated by nominal visit and treatment group.

#### **3.3.2.5 24 Hours Urine Collection (Tables 3.27.1 to 3.33. 3)**

Summary statistics, namely mean (sd), median, q1, q3, minimum, and maximum for Proteins, Creatinine, Sodium, Urea, Glucose, Phosphate and Osmolality will be tabulated by nominal visit and treatment group.

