The secondary objectives are to compare, among the two groups, absolute and relative changes in renal and liver volume parameters (at month 0, 12 and 36) as well as in functional and biochemical parameters by quarterly clinical visits during the 36 month follow-up. In particular, the following parameters will be assessed:

- Total kidney volume (at 3-years)
- Total renal cyst volume\*
- Total renal parenchyma volume\*
- Total renal intermediate volume\*
- Total liver and liver cyst volumes\*

*\*When feasible, by minimized radio contrast agent administration during CT acquisition*

- GFR decline (as assessed by serial measurements of the plasma iohexol clearance at month 0 and, every 6 months thereafter)
- Slope of eGFR (by MDRD 4 variable equation)
- Progression to the combined end point of doubling of serum creatinine and/or ESRD (*ESRD: need for chronic renal replacement therapy by dialysis or transplantation established on the basis of standard clinical criteria*)
- Progression to ESRD considered as a single endpoint
- Systolic, diastolic and mean blood pressure
- 24 h urinary protein excretion rate (at month 0 and every six months thereafter)
- Urinary osmolality (assessed from urine sodium, urea and glucose concentration on 24 hr urine samples)
- Morning spot urine sample (proteins, albumin, creatinine)
- Serum Insulin Growth Factor-1 (IGF-I)
- 24 h urinary phosphorus, creatinine and creatinine clearance
- Gallbladder sand/stones and renal stones (by ultrasonography).

In a subgroup of patients referred to the Clinical Research Center for Rare Diseases 'Aldo e Cele Daccò' and/or other institutions where these evaluations are feasible the

following other secondary objectives are to compare, among the two groups the quality of life and the societal costs by submitting to consenting patients a *Quality of life (QoL) Questionnaire* - Version 1 of SF-36 (QoL SF-36 V1™ Questionnaire) validated in Italy – and a *Short-Form-Health and Labour Questionnaire (SFHLQ)*. (See Appendix 2).

Furthermore, for exploratory purposes only, the treatment effect on endothelin and MCP-1 urinary excretion rate (overnight urine sample), in a subgroup (pending on study findings and fund availability).

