**Population: Full Analysis Set**

[Note: Tables 3.9.1-3.25.3, 3.26.1-3.26.3, 3.27.1-3.33.3, 3.34.1-3.38.3, 3.39.1-3.39.3, 3.40.1-3.40.3, 3.41.1-3.44.3, 3.45.1-3.49.3, 3.50.1-3.51.3, will be displayed as Table 3.8.1]

Table 3.52 Estimated Glomerular Filtration Rate using MDRD formula (eGFRmdrd) at baseline, 6-month, and 1-year, 2-year and 3-year follow-up in the study group as a whole (Overall), and in the two strata (CCC absent or CCC present) considered separately according to treatment with Octreotide-LAR or placebo.

| OCTREOTIDE-LAR |                              |                        |                        |                        |                        |                        |                        |                        |
|----------------|------------------------------|------------------------|------------------------|------------------------|------------------------|------------------------|------------------------|------------------------|
|                |                              | Baseline
(n=xx)     | 6 mo
(n=xx)         | 1 yr
(n=xx)         | 2 yrs
(n=xx)        | 3 yrs
(n=xx)        | Baseline
(n=xx)     | 6 mo
(n=xx)         |
| Overall        | Actual value*                | xx.x
[xx.x to xx.x] | xx.x
[xx.x to xx.x] | xx.x
[xx.x to xx.x] | xx.x
[xx.x to xx.x] | xx.x
[xx.x to xx.x] | xx.x
[xx.x to xx.x] | xx.x
[xx.x to xx.x] |
|                | Total Slope°
0-3 yrs      |                        |                        |                        |                        | xx.x
[xx.x to xx.x] |                        |                        |
|                | Chronic slope°
6 mo-3 yrs |                        |                        |                        |                        | xx.x
[xx.x to xx.x] |                        |                        |
| CCC
absent  | Actual value*                | xx.x
[xx.x to xx.x] | xx.x
[xx.x to xx.x] | xx.x
[xx.x to xx.x] | xx.x
[xx.x to xx.x] | xx.x
[xx.x to xx.x] | xx.x
[xx.x to xx.x] | xx.x
[xx.x to xx.x] |
|                | Total Slope
0-3 yrs       |                        |                        |                        |                        | xx.x
[xx.x to xx.x] |                        |                        |

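### Secondary blood pressure, urine, IGF-I and creatinine clearance objectives call for a between-arm comparison of changes, but the SAP only tabulates visit levels by arm

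*Supplement*

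**What the plan says.** The sentence in Section 1 (Introduction) that sets out the secondary objectives opens with "The secondary objectives are to compare, among the two groups, absolute and relative changes in renal and liver volume parameters (at month 0, 12 and" and, after giving month 36 as the last imaging time, continues "as well as in functional and biochemical parameters by quarterly clinical visits during the 36 month follow-up". The list below it names three blood pressure measures (mean, systolic and diastolic), six-monthly protein excretion, osmolality derived from the 24-hour collection, spot-urine protein, albumin and creatinine, serum IGF-I, and 24-hour phosphorus, creatinine and creatinine clearance.

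The analysis of these parameters is in Sections 3.3.2.1 to 3.3.2.6. Each gives the same plan: mean (sd), median, quartiles, minimum and maximum at each visit, by arm. For the 24-hour urine tests (3.3.2.5) the wording is "Phosphate and Osmolality will be tabulated by nominal visit and treatment group". For vital signs (3.3.2.1, Blood Pressure, Pulse Rate and Weight) it is "mean arterial pressure, pulse rate and weight, will be tabulated by nominal visit and treatment group". None of the six sections mentions a change from baseline, a model, a test, a difference or a confidence interval.

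The shells for Tables 3.3.1 to 3.8.1 match this text: levels at each visit in two arm columns. A note after Table 3.8.1 lists later tables and says of them, "3.45.1-3.49.3, 3.50.1-3.51.3, will be displayed as Table 3.8.1".

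**The concern.** The objective defines the quantity of interest as a change, and the task as a comparison between arms. The planned output contains neither. If the SAP is followed literally, the trial reports no treatment effect on blood pressure, proteinuria, albuminuria or IGF-I, although all are stated secondary objectives.

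Two things follow. Either readers compare columns of visit means by eye, without using the Visit 2 value collected in each patient, or someone chooses a comparison after the data are seen, which is what an SAP is meant to prevent. Late visits are harder to read by eye still. Section 3.2 excludes imputation in the Full Analysis Set, and Table 1.3 lists ESRD as a reason for withdrawal, so a month-36 column describes the patients who remain.

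**Working it through.** The documents state no figure on this point, so there is none to reproduce. The check sets the objective beside the analysis text and then counts what is affected.

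**1. Parameters covered, counted by table number.** The last column is what Section 1 names.

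| SAP section | Tables | Parameters | Named in Section 1 |
|---|---|---|---|
| 3.3.2.1 vital signs | 3.3–3.7 | 5 | 3 (systolic, diastolic, mean pressure) |
| 3.3.2.2 serum creatinine | 3.8 | 1 | 0 |
| 3.3.2.3 hematochemistry | 3.9–3.25 | 17 | 1 (IGF-I) |
| 3.3.2.4 creatinine clearance | 3.26 | 1 | 1 |
| 3.3.2.5 24-hour urine | 3.27–3.33 | 7 | 4 (protein, creatinine, phosphate, osmolality) |
| 3.3.2.6 spot urine | 3.34–3.38 | 5 | 3 (protein, albumin, creatinine) |

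Parameters: 5 + 1 + 17 + 1 + 7 + 5 = 36. Named: 3 + 0 + 1 + 1 + 4 + 3 = 12. The other 36 − 12 = 24 are not listed individually as secondary parameters.

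**2. Is a comparison supplied elsewhere in the SAP?**
- Section 3.2 says that tests are two-sided and that assumptions will be checked. It assigns no test or model to these parameters.
- Safety Tables 4.13 to 4.18 summarise change from baseline for serum creatinine, urea, calcium, sodium, potassium and phosphorus. They are descriptive, and none of the twelve named parameters is among them.

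**3. What the SAP does where it intends changes or comparisons.**
- Sections 3.3.2.7 and 3.3.2.8 ask for absolute and percent changes in TKV and htTKV, and Table 3.1.1 has p-value rows against placebo at 1 and 3 years.
- Section 3.3.1.2 compares measured GFR slopes by the Wilcoxon test, with a Hodges-Lehmann difference and 95% CI.
- Section 3.3.3.1 gives a Cox hazard ratio with 95% CI for ESRD and for the composite.
- Section 3.3.2.11 (total eGFR slope) and the chronic-slope section after it promise results of analyses but name no between-arm method.

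The gap is therefore confined to Sections 3.3.2.1 to 3.3.2.6, with a lesser gap in specification for eGFR slopes.

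**4. What baseline adjustment would gain.** Assume equal variances and a baseline/follow-up correlation r. The ratio of the standard error for a difference in raw follow-up levels to that from ANCOVA is 1/√(1 − r²):
- r = 0.6: 1/√0.64 = 1.25
- r = 0.7: 1/√0.51 = 1.40
- r = 0.8: 1/√0.36 = 1.67
- r = 0.9: 1/√0.19 = 2.29

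These correlations are assumptions, since the documents give none. The SAP also plans no formal comparison of raw levels. The figures show what a reader working from the tables would forgo, not a loss built into a planned test.

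**The case against.** The strongest reply is that descriptive reporting of a large laboratory panel is sensible. If all 36 parameters were tested at 0.05, the chance of at least one false positive under independence would be 1 − 0.95^36 = 0.84. That stands, and it is why the remedy should cover only the named parameters and give estimates with intervals rather than blanket tests. It does not excuse the twelve that Section 1 singles out for comparison.

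A second reply is that Table 3.8.1 shows mean, sd and n at each visit, so an unadjusted difference and interval can be worked out, and that chance baseline imbalance under randomisation costs precision rather than creating bias. Both statements are true. The calculation would still be the reader's own, unadjusted, and about levels rather than changes.

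A third is that the main trial protocol is not shown and may treat secondary comparisons. It may, but this SAP restates the objective and has its own sections and shells for these parameters, so the mismatch is internal to it.

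A reader might go further and infer from the shells that eGFR slopes get no comparison either. The documents do not support that. The slope sections list analyses separately from summary statistics. The slope shells are cut off on the page, so any further columns cannot be seen. The note after Table 3.8.1 is a loose formatting instruction: it also covers Tables 3.39 and 3.40, for which the text requires changes. The measured GFR shell shows no difference in its visible part, yet Section 3.3.1.2 specifies one.

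**Conclusion.** The point holds for the functional and biochemical parameters that Section 1 names. Twelve parameters have a stated objective of comparing changes and a plan that delivers neither a change nor a between-arm estimate. That conclusion rests on the SAP text alone. For eGFR slopes the fair statement is that the between-arm method is unspecified.

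Two wider inferences should be resisted. It would be wrong to say that the secondary endpoints as a whole lack a comparison: TKV, htTKV, ESRD and the composite have one. It would also be wrong to say that the plan throws away a given share of the patients. The ratios of 1.25 to 2.29 depend on assumed correlations and on a comparison that the SAP does not propose.

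The primary analyses are untouched. The change should be made because the stated secondary objectives cannot be met as the plan is written, and the data to meet them are already being collected.

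**What to change.** In Section 3.3.2, for the parameters named in Section 1 only:
- Add change from Visit 2, using log-ratio or percent change for proteinuria and albuminuria.
- Give the between-arm difference with 95% CI at months 12 and 36, from ANCOVA or a repeated-measures model with the baseline value and the CCC stratum as covariates.
- Label these estimates supportive and not controlled for multiplicity.

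State that eGFR slopes are compared by the Wilcoxon and Hodges-Lehmann method already given for the measured GFR slope. Amend the note after Table 3.8.1 so that the affected tables carry change, difference and interval. The rest of the laboratory panel can stay descriptive.

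If description is all that is intended, rewording the objective in Section 1 would also remove the contradiction, at the price of giving up the treatment estimates.

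The cost is SAP wording and programming. No new measurements are needed: the case report form already records these measurements, and the components of osmolality, at Visit 2 and at the month-12 and month-36 visits. The downside is 12 × 2 = 24 more supportive estimates per analysis set to report and interpret with restraint.
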